## Methods/design

### Design

The study is a non-inferiority, single-blinded randomized controlled trial with two arms, comparing the effectiveness of two training strategies for the THP. Consolidated Standards of Reporting Trials (CONSORT) guidelines [18] will be followed in the design, implementation and reporting of this randomized controlled trial.

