### Sample size estimation

The primary outcome of the study is the mean competence scores post training and at 3 months. We define non-inferiority as a difference of 5 points or less (corresponding to a 10 % difference on the outcome measure score) in the mean competence score between the two groups. A sample size of 80 LHWs (40 LHWs per arm) will have 99 % power to detect a 5-point margin with a 0.05 one-sided alpha level. Even after potential attrition in this area, at 3 months we will need 30 health workers in each group for a power of 80 % and a two-sided alpha error of 0.05.

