#### Primary outcome – competence of health workers

Primary outcome will be measure of LHW competence in the two groups. Equivalence is defined as a difference of less than 5 points (10 %) in the mean score of the competence measure across the two groups.

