#### Statistical analysis

The competence scores of the two groups will be compared using Student’s *t* test post training and at 3 months. A difference of less than 5 points between the two groups will be interpreted as supporting the non-inferiority hypothesis. We will also examine whether the competence scores improve at the 3-month mark after supervision. Stata software will be used for this. Qualitative data will be analyzed using framework analysis and manual software for qualitative studies. Cost-effectiveness will be assessed by combining costs with the primary outcome measure in incremental cost-effectiveness analysis. In addition, repeat re-sampling from the costs and effectiveness data (bootstrapping) will be used to calculate the probability that each of the training methods is the optimal choice, subject to a range of possible maximum values (ceiling ratio) that a decision-maker might be willing to pay for a unit improvement in ENACT score. A cost-effectiveness acceptability curve will be presented by plotting these probabilities for a range of possible values of the ceiling ratio [26].

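### Non-inferiority is judged on the observed mean difference alone, so at each assessment a TACTS arm truly 5 points worse passes half the time instead of 5%

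*Protocol article*

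**What the plan says.** All references are to the protocol article.

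- Design: "The study is a non-inferiority, single-blinded randomized controlled trial with two arms".
- Sample size estimation: "We define non-inferiority as a difference of 5 points or less", with 40 LHWs per arm giving 99% "power to detect a 5-point margin with a 0.05 one-sided alpha level". The next sentence asks for 30 per arm at 3 months for 80% power, now with "a two-sided alpha error of 0.05".
- Primary outcome: "Equivalence is defined as a difference of less than 5 points", again in terms of the mean score.
- Statistical analysis: "The competence scores of the two groups will be compared using Student’s *t* test post training and at 3 months". The decision rule follows at once: "A difference of less than 5 points between the two groups will be interpreted as supporting the non-inferiority hypothesis".

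For this comparison, no section mentions a confidence interval, a confidence limit or a test whose null is set at the margin.

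**The concern.** The null hypothesis of a non-inferiority trial is that TACTS is worse by at least the margin, here a true deficit of 5 points or more. Rejecting it requires evidence that accounts for sampling error. An observed deficit below 5 does not do that. The t test beside the rule does not help as described: a plain comparison of two groups tests a zero difference, and a non-significant result there does not show non-inferiority.

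The alpha and power in the sample size section belong to a test against the 5-point margin. The analysis section does not describe that test, so the error rate the trial was sized for is not the error rate of the rule that decides it. That rule settles the primary objective, and the case for scaling up TACTS rests on it.

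**Working it through.** **Inputs.** From the protocol: margin 5 points; 40 per arm at the start and 30 per arm at 3 months; alpha one-sided 0.05 in one sentence and two-sided 0.05 in the next. No SD of the ENACT score is given, so it has to be assumed. I take the values implied by the protocol's own power statements.

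**Step 1. The protocol's power figures.** Without an SD, the 99% cannot be reproduced directly. Solving the noncentral-t power of a two-sample test against a 5-point margin (true difference 0) for the SD gives:

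- 40 per arm, one-sided 0.05, 99% power: SD 5.58
- 30 per arm, two-sided 0.05 (0.025 in the non-inferiority direction), 80% power: SD 6.80

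A normal approximation gives 5.63 and 6.91, which changes nothing material. The two statements do not imply the same SD, so both are carried forward as a range.

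**Step 2. Standard errors.** SE = SD × √(2/n).

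- 40 per arm: 5.58 × √(2/40) = 1.248
- 30 per arm: 6.80 × √(2/30) = 1.755

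**Step 3. Chance that the written rule passes.** Let D be the observed deficit (specialist minus TACTS) and d the true deficit. Then P(D < 5) = Φ((5 − d)/SE).

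| True deficit d | 40 per arm, SD 5.58 | 30 per arm, SD 6.80 |
|---|---|---|
| 5 | Φ(0) = 50% | Φ(0) = 50% |
| 6 | Φ(−0.80) = 21% | Φ(−0.57) = 28% |
| 7 | Φ(−1.60) = 5% | Φ(−1.14) = 13% |

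The 50% holds by symmetry and does not depend on the SD. Simulation over SDs of 4 to 10 at both sample sizes gave 0.498 to 0.501. Reading the rule as an absolute difference below 5 leaves it at 50%.

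**Step 4. What a margin test would require.** It passes if D + t × SE < 5, so the largest passing deficit is 5 − t × SE.

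| Limit used | 40 per arm | 30 per arm |
|---|---|---|
| One-sided 95% | 5 − 1.665 × 1.248 = 2.92 | 5 − 1.672 × 1.755 = 2.07 |
| One-sided 97.5% | 5 − 1.991 × 1.248 = 2.52 | 5 − 2.002 × 1.755 = 1.49 |

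With the one-sided 95% limit, the pass rate is 5% at a true deficit of 5 and about 1% at 6. With the 97.5% limit it is 2.5% at a true deficit of 5. An observed deficit between these cut-offs and 5 is inconclusive, yet the written rule counts it as support. For example, an observed deficit of 4 at 40 per arm has a one-sided 95% upper limit of 4 + 1.665 × 1.248 = 6.08, well beyond the margin.

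**Step 5. Two time points.** The 50% is per assessment, and the article does not say how the two are combined. At a true deficit of 5 on both, requiring both to pass gives 25% to 50%, and accepting either gives 50% to 75%, depending on their correlation. Neither is near 5%.

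**The case against.** The strongest defence is that the sentence is shorthand. The one-sided alpha in the sample size section suggests that a test against the margin was intended, a t test can be run against a shifted null, and an unseen analysis plan may hold the formal rule. The statements under sample size and primary outcome can also be read as definitions of the margin, about the true difference.

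Part of this stands. Those two statements could be margin definitions, so the point rests on the Statistical analysis section, which says how results will be interpreted. The 50% applies to that rule as literally written. The shorthand reading does not rescue it, because the article states an explicit criterion and does not merely leave one out. An analysis plan using a confidence limit would contradict the published criterion.

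Two further cautions are fair. First, TACTS being significantly worse yet non-inferior is not in itself a fault, because a correct rule allows it: at 40 per arm and SD 5.58, an observed deficit of 2.7 has two-sided p = 0.03 and a one-sided 95% upper limit of 4.78. Second, not every positive result would be unsound, since an observed difference near zero would pass a proper test too at the implied SDs.

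**Conclusion.** The concern holds and must be fixed. As written, the rule does not control the false non-inferiority rate: 50% per assessment at a true deficit equal to the margin, against the planned 5% (2.5% under two-sided 0.05). That figure needs no SD; it needs only the literal reading and a symmetric sampling distribution of the difference. The other sizes, 21% to 28% at a true deficit of 6 points and 5% to 13% at 7, rest on the assumed SDs of about 5.6 and 6.8.

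**What to change.** Replace the decision sentence in Statistical analysis with: TACTS is non-inferior if the lower limit of the confidence interval for the mean ENACT difference (TACTS minus specialist) lies above -5. Choose one alpha. Use the two-sided 90% interval if it is one-sided 0.05, or the two-sided 95% interval if two-sided 0.05 is kept. Report the estimate with that interval. State that neither a point estimate inside 5 points nor a non-significant t test is evidence of non-inferiority. Align the wording under Sample size estimation and Primary outcome, and say whether the rule must be met at both assessments or at one named assessment.

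The cost is a few sentences and no extra data, and the article reports that enrollment has not begun. The criterion becomes harder to meet, but it is the one the stated power assumes. At SD 5.58 with 40 per arm and no true difference, power is 99% at one-sided 0.05 and about 98% at one-sided 0.025. At SD 6.80 with 30 per arm it is about 88% and 80%.

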#### Data management

Data management will be done by the Human Development Research Foundation (HDRF). All participating raters will hand over their collected information to the field coordinator. Data will be checked by the field coordinator on site for plausibility, consistency, and completeness. Any missing data or inconsistencies will be reported back to the assessor and clarified. Unique identification (ID) numbers will be used and individual LHWs will not be identifiable in the dataset. Data will then be exported and stored, and backed up on a secure server at the HDRF.

#### Ethical considerations

The study protocol was approved by the Ethics Committee of the Human Development Research Foundation, Pakistan (IRB/001/2015). The Ethics Committee is registered with the Office for Human Research Protection (OHRP), Rockville, MD, USA. The committee stated that there are no legal or ethical concerns to the planned procedures. The trial was registered in the ClinicalTrials.gov, 2016 (Identifier: NCT02644902).

#### Trial management

The trial management will be overseen by two committees: (1) the Trial Management Committee (TMC), which will monitor all aspects of conduct and implementation of the trial and its progress. The TMC will meet weekly initially, especially during the startup phase of the trial, and every second week thereafter if they decide it to be necessary. Minutes of TMC meetings will be kept; (2) the Trial Steering Committee (TSC) will chart the overall progress of the trial and will also provide technical input on the overall trial protocol. The TSC will also oversee trial participant’s safety and data monitoring. The TSC will meet every 6 months and minutes of key decisions will be maintained. The TMC is composed of the principal investigator (PI), co-investigators, data manager/trial manager, and the site team (research associate and field coordinators). The TSC is composed of the PIs, study co-investigators, the trial manager, and the study statistician. The TSC must agree on the final trial protocol and any protocol amendments and will provide advice on all aspects of the project. Decisions about any substantial amendments to be made to the protocol will be the responsibility of the TSC.

#### Ethical considerations

The study has been granted ethical approval from the Ethics Committee of the HDRF. Any updates/amendments made to the trial protocol will be shared with the Ethics Committee. For enrollment informed consent is mandatory (written or witnessed if the participant is illiterate). The confidentiality of personal data will be protected through data anonymity and through procedures to separate study data and participant identifiable data. If a woman is found to be seriously depressed by the LHWs, she will be referred to a psychiatrist and this will be reported to the Ethics Committee of the HDRF.

## Discussion

The development of THP-TACTS is an innovative and comprehensive approach to improving the scale-up and implementation of THP in the community. Developing such technology-assisted tools creates an opportunity to train CHWs at scale and to substantially increase the number of women with depression who do not have access to specialists in mental health. A demonstration of the effectiveness of TACTS in attaining health worker competence through this research study may result in greater availability of this technology not only in other humanitarian settings but also where access to mental health services is an issue. TACTS, if cost-effective in the long term, will help to strengthen the capacity of primary care systems to address multiple health priorities using technology. To our knowledge, this is the first effectiveness study on the technology-based training of CBT and THP for perinatal depression by a non-specialist. Additionally, as a feasibility study we will document any barriers to acceptability of this training program, enabling us to develop guidelines that will maximize successful implementation of the program in the future.

## Trial status

Enrollment for the trial has not yet started.

## Abbreviations

TACTS: Technology-assisted Cascade Training and Supervision
CHWs: community health workers
ENACT: ENhancing Assessment of Common Therapeutic factors
HDRF: Human Development Research Foundation
LHS: Lady Health Supervisor
LHW: Lady Health Worker
LMICs: low and middle income countries
mnGAP: mental health Gap Action Program
THP: Thinking Healthy Program
